### Home-based exercise intervention

2.5

Home-based supervised exercise training will consist of two different exercise modalities, Moderate Intensity Continuous Training (MICT) and High Intensity Interval Training (HIIT) (37), with individually adapted intensities based on the results from the exercise testing. Each exercise period will consist of six weeks with an eight-week washout in-between, starting with MICT. The exercise periods start and end with exercise testing (Figure 2).

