**Figure 2 F2:**
[figure not shown]
The feasibility study, with a cross-over design including test-points, exercise training periods, wash-out, and timepoints of the interviews.

The MICT exercise training will consist of moderate intensity/longer (60%Wpeak) duration exercise (37) carried out three times per week—Tuesday, Thursday, and Saturday during the three-week period of supervision via video conferencing, and at timepoints chosen by the child with at least one day in between sessions during the periods of video-supervision. Exercise will consist of continuous biking at 60%Wpeak for a total time of 30 min (Figure 2).

The HIIT exercise training will begin by using a protocol consisting of bouts of high-intensity (95%Wpeak) exercise lasting for 60 s (37). These bouts will be interspersed by four minutes of low-intensity (40%Wpeak) exercising (37). There will be five bouts per session, with the same weekly plan as for MICT (Figure 2).

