#### Feasibility analysis

2.9.1

To structure the feasibility analysis process, scientific, management, and resource (33) uncertainties will be assessed (Table 1). The analysis will have an intent-to-treat (ITT) approach where above 66% of successful cases will be considered feasible, adjustable if successful cases fall between 20% and 65%, and unfeasible if the successful case rate is below 20%, both for individual outcomes and for an overall analysis. Wide thresholds were chosen to allow for iterative refinement of the intervention based on participatory feedback during study. When items are considered adjustable, the data collected from the android tablet computer, field notes, and interviews will be used to further develop the HOME-EX protocol.

**Table 1 T1:** Description of predefined progression criteria.

Items	Outcomes	Predefined progression criteria
***Process:*** This assesses the feasibility of the processes that are key to the success of the main study. Evaluation of study design (e.g., reducing uncertainty around recruitment, data collection, retention, outcomes, and analysis)		
Recruitment	Recruitment rate	>66% of invited participants accepted to participate in the study
		65%–20% of invited participants agreed to participate in the study
		<19% of invited participants agreed to participate in the study
Retention	Retention rate	>66% completed all exercise periods
		65–20% completed all exercise periods
		<19% completed all exercise periods
Data collection	Completion rate and perceived usefulness	>66% completed all procedures and are perceived as useful/acceptable
		65%–20% completed all procedures and perceived them as useful/acceptable
		<19% completed all procedures and perceived them as useful/acceptable
Outcome measures	Variance and distribution of collected data	Outcomes provide interpretable data with acceptable variance
		Outcomes partially interpretable, large variance
		Outcomes are not interpretable, excessive variance
***Scientific:*** This deals with the assessment of treatment safety, dose, response, effect, and variance of the effect (study design)		
Outcome measures	Variance and distribution of collected data	Outcomes provide interpretable data with acceptable variance
		Outcomes partially interpretable, large variance
		Outcomes not interpretable, excessive variance
Acceptability	Perceived acceptability of the eHealth tablet app and home-based exercise	>66% report app/exercise acceptable

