		65%–20% report app/exercise acceptable
		<19% report app/exercise acceptable
Usability/technical demands	Technical support needed	Only initial introduction needed
		Required equal time for support as for tablet app use
		Unable to use eHealth app due to technical demands
Barriers/facilitators	Perceived barriers and facilitators when exercising and using eHealth tablet app	Perceived more facilitators than barriers
		Equal numbers of facilitators as barriers
		Perceived more barriers than facilitators
***Management:*** This covers potential human and data management problems		
Capacity to deliver exercise sessions	Trainers' capacity to deliver exercise intervention	>66% completed exercise sessions
		65%–20% completed exercise sessions
		<19% completed exercise sessions
Capacity to deliver exercise equipment	Logistics in delivering cycle ergometers to children's homes	>66% successful deliveries
		65%–20% successful deliveries
		<19% successful deliveries
***Recourses:*** This pertains to assessing time and resource problems that can occur during the main study		
Resources to deliver	Exercise intervention	Trainer reports delivery of exercise sessions as feasible with given resources
		Trainer reports delivery possible but challenging
		Provider reports delivery not feasible
Resources to deliver	Effectiveness testing	The coordination of all tests is feasible within resources
		The coordination of all tests is possible but challenging
		Provider reports delivery not feasible
Resources to deliver	Logistics to deliver cycle ergometers to children's homes	The coordination of all tests is feasible within resources
		The coordination of all tests is possible but challenging
		Provider reports delivery not feasible

Process uncertainties will include as recruitment rate, retention rate, acceptability, usability, barriers/facilitators, and adherence. Scientific uncertainties will include safety, dose, and variance of effect, all aspects related to the study design planned for a future efficacy study, Management uncertainties will address data collection processes, while resource-related uncertainties will assess the time and resource problems involved in running the study (33) (see Table 1 on progress criteria).

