The present feasibility study has limitations that should be considered when interpreting the findings. The small sample size, although appropriate for feasibility testing (36), limits the ability to capture population variability and reduced generalisability. Recruitment of children who are TD through social media platforms may introduce selection bias and potentially limit participation to families with higher literacy or access to online networks (49). The comprehensive testing procedures, including blood samples, may increase participation burden and may influence adherence and retention leading to attrition bias (50). Additionally, in the present study HIIT and MICT periods are not randomized. The absence of randomisation and the sequential design may introduce order and carryover effects in subsequent studies, reducing their internal validity. Finally, wide threshold may overestimate feasibility (51), while participatory design (31) may introduce variability in intervention delivery, reducing standardisation and reproducibility.

Taken together, these limitations highlight potential biases and methodological challenges that should inform the design of subsequent studies. The present feasibility study represents an early step in the research process. A subsequent pilot study is planned if this feasibility study holds promising results. The pilot study will allow for more rigorous testing of procedures and preliminary effectiveness testing. A more stringent feasibility threshold is likely to be applied in the pilot study.

If the present feasibility study and the pilot study show promising results, a larger study evaluating the physiological effectiveness and the cost-effectiveness of HIIT and MICT should consider recruitment from a larger area. This further emphasises the importance of a comprehensive feasibility study.

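### Table 1 gives one acceptability verdict for app and exercise together, and scores neither acceptability nor session completion by MICT and HIIT

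*Protocol article*

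**What the plan says.** Section 2.9.1 sets three bands: feasible above 66% successful cases, adjustable from 20% to 65%, and "unfeasible if the successful case rate is below 20%, both for individual outcomes and for an overall analysis". It states an intention-to-treat approach and ties the use of tablet data, field notes and interviews to items found adjustable.

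Two rows of Table 1 matter here.

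- **Acceptability.** The outcome is "Perceived acceptability of the eHealth tablet app and home-based exercise", and the feasible band is ">66% report app/exercise acceptable".
- **Capacity to deliver exercise sessions.** This row sits under Management, its outcome is the trainers' capacity to deliver, and the feasible band is ">66% completed exercise sessions".

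Neither row mentions modality or period. Section 2.5 describes two modalities, MICT and HIIT, and fixes their order: "Each exercise period will consist of six weeks with an eight-week washout in-between, starting with MICT". MICT is "carried out three times per week" (section 2.5, text after Figure 2), and HIIT follows the same weekly plan. The opening of section 2.9 lists the exercise intervention and the ability of the eHealth solution to deliver it as separate things to assess. The Discussion looks ahead, after a pilot, to "a larger study evaluating the physiological effectiveness and the cost-effectiveness of HIIT and MICT".

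**The concern.** A progression criterion should give a verdict on something that can be kept, changed or dropped. Here the separable parts are the app, the MICT programme and the HIIT programme. The acceptability row joins the app to the exercise without saying how a child who accepts one and not the other is counted. Neither row asks for a result by modality, so a good result in one period can be averaged with a poor one in the other.

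What is at stake is the recorded verdict passed on to the pilot and the later study. A single entry of feasible could stand over a HIIT programme that, judged alone by the same bands, needs adjustment. Likewise, a well-liked app could stand in for an exercise programme that fewer than half of the children accept.

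**Working it through.** The plan derives no figure here; its cut-offs are set by choice. The check is therefore a count from its own inputs.

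**Inputs.** 20 children are anticipated (section 2.3). There are two periods of 6 weeks, one per modality (section 2.5), with 3 sessions a week in each. The bands are those of section 2.9.1. Assumptions: all 20 children enrol, all planned sessions are in the denominator, and the two periods carry equal weight.

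**1. The slash.** Suppose 19/20 accept the app (95%) and 9/20 accept the exercise (45%).

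- Read as either: at least max(19, 9)/20 = 95%, feasible.
- Read as both: at most min(19, 9)/20 = 45%, and at least (19 + 9 − 20)/20 = 40%, adjustable.

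The same answers give different verdicts. Under the both reading, a liked app cannot hide disliked exercise, but MICT and HIIT are still not separated.

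**2. Acceptability over the two periods.** Suppose 18/20 accept MICT (90%) and 9/20 accept HIIT (45%). Over 40 child-period ratings this is (18 + 9)/40 = 67.5%, feasible. HIIT alone is adjustable.

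**3. Session completion over the two periods.**

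- Sessions per modality: 20 × 6 × 3 = 360; total 720.
- Exceeding 66% of 720 (475.2) takes 476 sessions, which is 66.1%.
- Lowest HIIT completion that still gives feasible = (476 − MICT sessions completed)/360.

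| MICT completed | HIIT sessions needed | HIIT completion |
|---|---|---|
| 360 (100%) | 116 | 32.2% |
| 324 (90%) | 152 | 42.2% |
| 288 (80%) | 188 | 52.2% |
| 252 (70%) | 224 | 62.2% |

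Every HIIT value in the last column is adjustable by the plan's own bands.

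**4. The limit of the masking.** HIIT below 20% means at most 71 of 360 sessions. With MICT at 100% the combined rate is (360 + 71)/720 = 59.9%. An unfeasible HIIT result can be lifted to adjustable on this row, but not to feasible.

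**5. Sensitivity to the denominator.** If the row counts only the three video-supervised weeks, each modality has 20 × 3 × 3 = 180 sessions. Exceeding 66% of 360 takes 238, and (238 − 180)/180 = 58/180 = 32.2%, as before. The Discussion mentions a fourth exercise period, whereas section 2.1 gives two. As long as MICT and HIIT periods are equal in number and size, the proportions in step 3 hold to within rounding.

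**The case against.** The strongest reply is that combining the periods is inferred. Table 1 omits a split; it does not order a merger. Each period is a single modality, questionnaires and interviews follow each one (section 2.8), and the team meets after each (section 2.9.4), so results by modality will exist. This stands, and it is why the arithmetic on modality is conditional. But Table 1 is where the progression criteria are fixed, and none of them uses that information by modality.

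A reader might go further in five ways that the documents do not support.

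- **A masked HIIT result would trigger no refinement.** Section 2.9.4 and the Discussion allow upcoming periods to be changed on participants' feedback, whatever the band. The rule for adjustable items is one route to refinement, not the only one.
- **HIIT would be judged only by the children who stayed.** Section 2.9.1 states intention to treat, and the retention row counts completion of all periods. Retention does not, however, register poor adherence or dislike among children who remain.
- **MICT comes first and is the easier period.** No passage calls it easier, and the arithmetic does not need it to be.
- **The session row measures children's adherence to HIIT.** It is labelled as trainers' delivery capacity. Section 2.9.1 lists adherence among the process uncertainties, but Table 1 has no row of that name, so completed sessions are the nearest count.
- **An unfeasible HIIT could be recorded as feasible.** Step 4 of the working rules this out for session completion.

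It is also fair to say that the study's summary judgement concerns whether the eHealth solution can deliver exercise at home, that the Discussion concedes that wide thresholds may overestimate feasibility, and that a pilot comes before any larger study. These points lower the stakes but do not make the row clearer.

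**Conclusion.** The point holds in a limited form. The ambiguity of the combined app and exercise criterion is in the text itself and can move the verdict from at least 95% to at most 45% on the same answers. The lack of scoring by modality is also in the text. Its consequence depends on the periods being combined: an adjustable HIIT result can then be recorded as feasible, with HIIT acceptability at 45% in the example or HIIT session completion down to 32.2% if every MICT session is completed. The examples show what the criteria permit; they are not forecasts. They assume 20 enrolled children, equal weight per period and all planned sessions counted. Per-period interviews, team meetings and the retention row reduce the risk without removing it. This is an inexpensive improvement to the progression criteria and does not undermine the study.

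**What to change.** Split the acceptability row into one row for the app and one for the exercise. Apply the existing bands for exercise acceptability and for completed sessions separately to the MICT period and the HIIT period. Keep all enrolled children in each denominator, in line with the stated intention-to-treat approach. Take each acceptability percentage from one fixed question per component in the questionnaire already given after each period, and use the interviews to explain it. Take completed sessions from the app records.

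With 20 children, feasible would then mean at least 14/20 (70%; 13/20 is 65%) for the app, for MICT and for HIIT, and at least 238/360 sessions (66.1%) in each period. MICT at 360/360 with HIIT at 116/360 would read as feasible and adjustable respectively, instead of a single feasible at 476/720.

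The cost is a few more rows in Table 1 and one fixed question per component, with no extra visits. The downside is fewer observations per verdict: 20 ratings instead of 40 and 360 sessions instead of 720, so one child moves an acceptability percentage by 5 points.

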According to the MRC methodological framework (32), feasibility testing is important, as it makes it possible to assess uncertainties; e.g., the predefined progression criteria, before potentially conducting a larger-scale effectiveness study (32). Within this feasibility study, several predefined progression criteria are set, in terms of quantitative outcomes. Recruitment and retention are well-known challenges in research, which is why progression criteria addressing these aspects are important. As the intervention is delivered in the participants home rather than in a fully equipped training facility, additional criteria addressing delivering, capacity, logistic, and resource demands are essential. Together, these criteria, in line with those described by Thanbane et al. (33), enable a focused assessment of feasibility prior to the progression to a potential future full-scale study. Qualitative outcomes collected from participants will be used when uncertainties are considered adjustable. Information from both quantitative and qualitative outcomes will be used to fine-tune the feasibility of the eHealth solution. When all outcomes are collected, a summary assessment will be conducted to determine the feasibility of the eHealth solutions to deliver an exercise intervention at the children's homes. Although one may argue there are many outcomes, all the outcomes together combine to enhance the understanding and determination of whether the intervention is feasible, thereby reducing the risk of conducting a large multi-centre effectiveness study that was not possible to perform.

The NASSS-CAT framework used for assessing the eHealth solution and the general conditions for implementing the intervention provide a nuanced and robust basis for the identification of risks and opportunities related to the project (34). In addition, the use of the NASSS-CAT framework (34) together with the MRC methodological framework (32) and the convergent mixed methods approach (30) enables the intervention to be examined from multiple perspectives. Altogether, these frameworks (32, 34) and methodological approach (30) support a comprehensive assessment of the complexity of the home-based exercise intervention.

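### In Table 1 the resource row for ergometer logistics carries the effectiveness-testing criteria, so its feasible and adjustable levels describe lab-test coordination instead of ergometer delivery

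*Protocol article*

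**What the plan says.** Table 1 in section 2.9.1 of the protocol article lists predefined progression criteria. Each row has an outcome and three levels, which correspond to the feasible, adjustable and unfeasible classes defined in the text above the table. The Resources block is introduced with "This pertains to assessing time and resource problems that can occur during the main study" and has three rows, all under the same item label about resources to deliver:

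- **Exercise intervention.** The top level is "Trainer reports delivery of exercise sessions as feasible with given resources".
- **Effectiveness testing.** The levels are "The coordination of all tests is feasible within resources", "The coordination of all tests is possible but challenging" and "Provider reports delivery not feasible".
- **Ergometer logistics**, whose outcome begins "Logistics to deliver cycle ergometers". The three levels are the same three sentences as in the testing row.

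The Management block of the same table has a separate row on ergometer logistics. It is scored by percentage, with a top level of ">66% successful deliveries", a middle band of 65%–20% and a bottom level below 19%.

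The Discussion explains that, because the intervention takes place at home and not in a training facility, "additional criteria addressing delivering, capacity, logistic, and resource demands are essential".

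**The concern.** The outcome of the row is one activity, and the two levels that matter most for its classification describe another. Section 2.4 keeps the activities apart: ergometers go to each child's home, while exercise testing is done in a laboratory at Lund University. How well the lab tests were coordinated says nothing about the effort of getting ergometers to homes.

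The classification has consequences. Section 2.9.1 applies the three classes to individual outcomes as well as to an overall analysis, and an adjustable rating is what brings in tablet data, field notes and interviews to develop the protocol further. The Discussion plans a summary assessment of all outcomes and suggests that a later, larger study consider recruiting from a larger area, where equipment transport would matter more. If the ergometer row is applied as printed, strained delivery logistics would not produce an adjustable rating through it. If the team instead reinterprets the row after seeing how deliveries went, the criterion is no longer predefined.

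**Working it through.** No arithmetic beyond counting is involved, and the plan states no figure to reproduce. The check is a line-by-line comparison.

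**Step 1: compare the two rows.**

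| Level | Testing row | Ergometer row | Identical? | Names tests? | Names ergometers, equipment or homes? |
|---|---|---|---|---|---|
| Feasible | "The coordination of all tests is feasible within resources" | same sentence | yes | yes | no |
| Adjustable | "The coordination of all tests is possible but challenging" | same sentence | yes | yes | no |
| Unfeasible | "Provider reports delivery not feasible" | same sentence | yes | no | no |

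All 3 levels are identical, 2 of 3 name the tests, and 0 of 3 name ergometers, equipment or homes.

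**Step 2: compare with the exercise-intervention row.** Its top level, "Trainer reports delivery of exercise sessions as feasible with given resources", names that row's own subject. The pattern of the block is therefore row-specific wording at the upper levels and a shared general sentence at the bottom. The ergometer row departs from that pattern.

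**Step 3: look for another criterion that fills the gap.** The only other ergometer row is in the Management block and is scored by the share of successful deliveries. It answers whether the ergometers arrived. The Resources block is meant to capture time and resource problems, which is a different question.

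**Step 4: apply the rows literally to two hypothetical outcomes.** In both, every ergometer is delivered (100%).

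| Situation | Management ergometer row | Resources ergometer row, as printed | Resources ergometer row, by its label |
|---|---|---|---|
| Lab tests run smoothly; deliveries strain the team | feasible | feasible | adjustable |
| Lab tests strain the team; deliveries are easy | feasible | adjustable | feasible |

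In each case the printed wording and the row's own label give different classes. In the first, neither ergometer row records the strain.

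**Step 5: count the rows.** Process 4 + Scientific 4 + Management 2 + Resources 3 = 13, counting the outcome-measures row once in each of the two blocks where it is printed. One row has levels about the wrong activity: 1 of 3 in Resources, 1 of 13 overall.

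**The case against.** The strongest reply is that the intention is plain. The outcome label names ergometer logistics, the neighbouring rows show the scale that was meant, and section 2.9.4 has the research team meet after each exercise period to discuss findings. A sensible team would hardly score deliveries by how lab testing went. This stands as an argument that the harm may not materialise. It does not make the printed criterion correct: a predefined criterion that has to be reinterpreted to make sense no longer fixes the decision in advance.

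A second reply is that ergometer logistics are covered in Management. That is partly right. A reader might infer that the plan has no ergometer criterion at all, and this would be wrong, because failed deliveries would show in the percentage row. The gap is the burden of deliveries that succeed.

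Other stronger readings are also not supported:

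- **The testing row is faulty too, making it 2 of 3.** Its lowest level speaks of delivery, but under an item label about resources to deliver, that can mean delivery of the testing. The same sentence closes all three resource rows. The testing row can be scored unfeasible on its own subject, and the ergometer row can use that level as well.
- **Test coordination is counted twice in the overall result.** Section 2.9.1 mentions an overall analysis, but these rows carry no percentages and no rule for tallying rows is given. Double weight is possible, not established.

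**Conclusion.** The point holds for the ergometer-logistics row in the Resources block: 1 of 3 resource rows and 1 of 13 rows in Table 1. Its feasible and adjustable levels concern test coordination, and only the general lowest level can apply to ergometers. As a result, the plan has no valid wording to separate feasible from adjustable for the time and resources that successful ergometer deliveries take, although its own Discussion treats such criteria as essential.

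The size is modest. No effect estimate and no percentage-based criterion is affected. The conclusion rests on reading the levels as printed and on taking lab testing and home delivery as separate activities, which section 2.4 supports. The sentences appear in full under their own row label, so text extraction is an unlikely explanation. A copying error in the table is the likely cause, but that is an inference.

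**What to change.** Reword the three levels of the ergometer row in the Resources block along these lines:

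- Feasible: *Delivery of cycle ergometers to homes is feasible within resources.*
- Adjustable: *Delivery of cycle ergometers to homes is possible but challenging.*
- Unfeasible: *Delivery of cycle ergometers to homes is not feasible within resources.*

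Optionally, for clarity, let the lowest level of the testing row say that coordination of the tests is not feasible within resources.

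Section 2.10 describes recruitment as in progress, so the change should be made and dated before feasibility outcomes are assessed; otherwise the reworded criterion cannot be called predefined. The cost is wording in one table, with no new data, staff or visits. The Management row on successful deliveries needs no change on account of this point.
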